### Randomization

Participants are randomized (1:1:1) to the control group or intervention groups stratified by time since chemotherapy completion, age and hormone therapy (Y/N). The randomization will be carried out by an independent researcher using random number lists created in MinimPy, a free, open-source application (http://minimpy.sourceforge.net/). Participants will be randomized by minimization, a covariate-adaptive randomization technique which balances the allocation to groups across specified covariates without compromising randomization [32].

After randomization, participants will be unblinded to group assignment, as the interventions do not allow for blinding. Assessors and statisticians will be blinded.

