### Analysis plan

Primary outcome measures:
The difference in mean change scores from the baseline on the CFQ between groups; andThe difference in mean change scores from the baseline on the connectivity in the attention network between groups.

Secondary outcome measures:
Changes in neurocognitive test scoresChanges in emotional distress, fatigue and mindfulness skillsChanges in brain white and gray matter structureChanges in functional brain activity during N-back taskChanges in functional connectivity during resting state; andChanges in biomarkers of inflammation

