### Data analysis

Analyses will be done both per protocol and intention to treat. Analyses are based on general linear modelling and multilevel mixed-effects modelling. The impact of the intervention will be tested (confirmatory) via a multilevel model with two levels (time points nested within persons). Results will be controlled for false discovery rate [48]. Predictors are time (level-1 predictor), condition (level-2 predictor) and cross-level interactions. To evaluate the process of change a mediation analysis will be performed. Mediation will be tested (exploratory) by adding potential mediators (e.g., different mindfulness facets) and their interaction with condition and time in the intervention model. Time practicing will be tested (exploratory) as a potential moderator. Models are based on the procedure described in Bauer et al. (2006) [49].

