State of the art image processing techniques will be used to analyze the MRI images and study both structural and functional differences longitudinally within the groups and between the groups. Voxel-based morphometry (VBM) will be used to study structural changes in the brain. Additionally, advanced multi-shell diffusion images will be processed and analyzed using ExploreDTI/Metrics (DTI, fixel-based analysis, CSD tractography), NODDI modelling software and in-house developed software. This will include head-motion and eddy-current correction and will use inverse phase encoding images and B0 maps for optimizing correction procedures. Seed-based analysis, independent component analysis (ICA) and graph theory will be applied to analyze the resting state fMRI data and assess brain connectivity. From the MRI data we will generate maps reflecting grey matter volume, white matter properties (e.g., fractional anisotropy, neurite density index, orientation dispersion index) and brain connectivity. Voxel-based statistical analysis using the general linear model and non-parametric statistics will be used to find significant differences (*p* < 0.05) in imaging parameter maps between time points and groups. Statistical parametric mapping on a voxel-by-voxel basis will be conducted by using a general linear model approach to assess brain activation during the N-back memory task. Contrast images comparing pairs of working-memory load conditions (e.g., 3-back > 0-back) will be created for each patient and will be used in second-level analyses to assess differences between time points and groups (confirmatory tests for H1 and H2, exploratory test for H3).

The association between the obtained outcomes, psychological and behavioral outcomes based on the scores of retrospective questionnaires, neuroimaging parameter maps, the performance on neurocognitive tests and biomarkers of inflammation will be investigated using correlation analysis.

The number of patients in this study (40 patients in each group) is based on: (1) earlier studies that investigated the effects of MBI on the brain in which effects where shown after MBI in groups of *n* = 20 (longitudinal design [50] and *n* = 13 (cross-sectional design) [51, 52]; (2) the one study that already investigated the impact of MBI on cognitive impairment after cancer treatment. This study reported an impact of MBI on cognitive functioning with a design of *n* < 40 in the different study arms [53].

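### The confirmatory model neither adjusts for baseline nor includes the three minimisation factors; the comparison stays unbiased, but precision is lost

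*Protocol article*

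**What the plan says.** All of this is in the protocol article.

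- **Analysis plan.** The first primary outcome is "The difference in mean change scores from the baseline on the CFQ between groups". The second is worded the same way for connectivity in the attention network.
- **Data analysis.** "The impact of the intervention will be tested (confirmatory) via a multilevel model with two levels (time points nested within persons"). The next statement on the model is its list of terms: "Predictors are time (level-1 predictor), condition (level-2 predictor) and cross-level interactions". The later additions, mediators and practice time, are labelled exploratory.
- **Randomization.** "Participants are randomized (1:1:1) to the control group or intervention groups", "stratified by time since chemotherapy completion, age and hormone therapy (Y/N"). The method is named: "Participants will be randomized by minimization, a covariate-adaptive randomization technique".
- **Design and Table 2.** The time points are T0, T1 (1 to 3 weeks after the intervention) and T2 (3 months after).

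Nothing in the article says that the confirmatory model adjusts for the T0 value, holds the T0 means equal across arms, or includes any of the three allocation factors.

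**The concern.** Two pieces of information that the design already provides are not used.

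First, at T0 the arms differ only by chance. A model with a free T0 mean in each arm spends information on estimating those differences and then subtracts them in full. Regressing on baseline subtracts only the part that predicts follow-up, so its variance is smaller whenever the correlation is below 1.

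Second, minimisation makes the arms alike on time since chemotherapy, age and hormone therapy. If these factors predict the analysed quantity, the true variability of the treatment contrast is smaller than an analysis that ignores them reports.

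Power is at stake. The sample size rests on precedent ("The number of patients in this study (40 patients in each group) is based on: (1) earlier studies") and no power calculation is shown, so there is no known margin to give away. One hypothesis also sets the mindfulness arm against an active comparator, where a smaller difference than against usual care is to be expected.

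**Working it through.** **Inputs.** From the article: 40 per arm, three arms, three time points, three minimisation factors, enrolment on a high CFQ score. Not in the article, hence assumed: two-sided alpha of 0.05 for the CFQ (the article gives p < 0.05 only for the imaging maps), the baseline-to-follow-up correlation r, and the share of variance that the minimisation factors explain. The figure of 40 per arm cannot be reproduced, because no effect size, SD or power is stated. Worked backwards, 40 per arm gives 80% power for (1.96 + 0.84) × √(2/40) = 0.626 SD of whichever variable is analysed.

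**Step 1: precision, equal variances.** In units of the raw variance, a change score has variance 2(1 − r) and a baseline-adjusted outcome 1 − r². The ratio is (1 − r²) / [2(1 − r)] = (1 + r)/2. Power is for a difference of 0.5 raw SD with 40 per arm.

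| r | variance ratio | change-score patients per arm worth 40 adjusted | power, change | power, adjusted |
|---|---|---|---|---|
| 0.5 | 0.75 | 40/0.75 = 53 | 0.61 | 0.73 |
| 0.6 | 0.80 | 50 | 0.71 | 0.80 |
| 0.7 | 0.85 | 47 | 0.82 | 0.88 |
| 0.8 | 0.90 | 40/0.90 = 44 | 0.94 | 0.96 |

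Example at r = 0.6: the SDs are √0.8 = 0.894 and √0.64 = 0.8. The standardised differences are 0.5/(0.894 × 0.2236) = 2.50 and 0.5/(0.8 × 0.2236) = 2.80. The powers are Φ(0.54) = 0.71 and Φ(0.84) = 0.80.

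**Step 2: selection on the CFQ.** Take a normal score cut at +1 SD; its remaining variance is v = 0.199.

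- *The screening score is also T0.* The regression slope is unchanged and the T0 variance shrinks to v. The ratio becomes (1 + r) / [(1 + r) + (1 − r)v]. At r = 0.5 this is 1.5/1.600 = 0.94; at r = 0.8 it is 1.8/1.840 = 0.98. The gain is worth 41 to 43 patients per arm.
- *T0 is measured separately after screening.* With k = r²(1 − v), the correlation among those enrolled is (r − k)/(1 − k): 0.37 at r = 0.5 and 0.59 at r = 0.8. The ratio (1 + r)/2 at these values is 0.69 and 0.79.

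The article does not say which applies. It sets the cut by a reference study and also admits patients on the extra CFQ questions, so +1 SD among those screened is itself an assumption.

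**Step 3: minimisation factors.** With exact balance, the unadjusted test runs at 2[1 − Φ(1.96/√(1 − R²))], where R² is the share of the variance of *change* that the factors explain: 0.039 at 10% and 0.028 at 20%. A simulation of the design (120 patients, three arms, minimisation on three binary factors with probability 0.8 for the best arm, r = 0.6, 3,000 runs) gave:

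- Factors predict level but not change: 0.049 to 0.050 for the change analysis, which is nominal.
- Factors explain 5%, 10%, 20% or 30% of the variance of change: 0.043, 0.041, 0.029 and 0.016. Adding the factors brought this to 0.048 to 0.053.
- Baseline added without the factors, at 10% and 20%: 0.030 and 0.022. Half of the remedy makes the conservatism worse.
- Power for 0.5 SD at 10%: 0.66 (change only), 0.69 (change plus factors), 0.72 (baseline only), 0.81 (both).

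**Step 4: which form of the remedy works.** This used two arms of 40, one follow-up, one perfectly balanced binary factor and r = 0.6, in two sets of runs (3,000 and 5,000). With T0 means constrained equal and the factor as a main effect only, type I error was 0.043 to 0.046 at 10% and 0.032 to 0.038 at 20%, still conservative. With factor-by-time added it was 0.052 to 0.057. With T0 as a covariate and the factor as a main effect (5,000 runs) it was 0.051 to 0.052.

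**The case against.** The strongest reply has four parts.

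- *The planned comparison is valid.* This stands. A reader might infer that leaving out the minimisation factors invalidates the test or inflates its error rate. The article gives no ground for that: stable effects of the factors cancel in a change score, conservatism arises only if they predict change, and no scenario showed inflation. Nothing in the article says whether they do predict change.
- *Baseline is in the model.* This also stands. A reader might infer that the T0 value is dropped. With time points nested within persons and T0 among them, it is a repeated outcome. What is missing is its use as a covariate or through a common-baseline constraint.
- *The gain for the CFQ may be small.* This stands in part. If the screening score serves as T0, selection leaves little to recover. If T0 is separate, the gain is larger than the simple formula suggests. A flat claim of 44 to 53 patients per arm for the CFQ is not supported.
- *The article is condensed, its term list does not say that it is exhaustive, and imaging has its own methods.* A fuller document may add covariates. Still, the article names this model as the confirmatory one, lists its predictors, and labels the additions that it does mention as exploratory. The imaging point stands: seed-based, independent-component, graph and voxel-wise analyses are planned, so this model may not govern every form of the connectivity outcome.

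**Conclusion.** The point holds as a loss of efficiency in a stated analysis. Under equal variances the adjusted variance is 0.75 to 0.90 of the change-score variance for assumed r of 0.5 to 0.8. For the CFQ the range is wider, about 0.69 to 0.98, depending on whether T0 is a fresh measurement or the screening score. Omitting the minimisation factors costs further power only if they predict change, with the test then running at about 0.04 (10% of the variance of change) or 0.03 (20%); otherwise it is nominal. The correlation, the explained share, alpha for the CFQ and the effective cut are all assumptions. The equality with the change-score difference is exact only for complete data with time as categories. This is worth changing because it is nearly free. It is not a flaw that undermines the trial's conclusions.

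**What to change.** Amend the predictor sentence in Data analysis. Make T1 and T2 the outcomes, with these fixed effects: the T0 value and its interaction with time, categorical time, condition, condition-by-time, and time since chemotherapy and age (both continuous) and hormone therapy (yes/no) as covariates.

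A near-equivalent alternative keeps T0, T1 and T2 as outcomes, constrains the T0 means to be equal across arms, and gives each minimisation factor an interaction with time. In that form main effects alone do not suffice (step 4). Baseline and factors should go in together.

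Apply the model to the CFQ, to the summary measure of attention-network connectivity where this multilevel model is used, and to the continuous secondary outcomes. It would also help to state whether the screening CFQ serves as T0.

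The cost is wording and a few degrees of freedom. Age, the CFQ and resting-state imaging are already collected at baseline, and the other two factors are needed for allocation. Under randomisation the quantity estimated, the between-group difference in mean change, is unchanged. Statisticians are to be blinded, so the change can be fixed before any unblinded look.

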## Background

The prevalence of cognitive impairment in cancer patients has become an important area of research. There is increasing evidence that chemotherapy treatment for breast cancer can have both acute and long-term effects on cognitive functioning [1, 2]. Women treated for breast cancer regularly self-report problems with cognitive processes involving memory, attention and executive functioning [3]. These cognitive deficits can be a worrying side effect of cancer and its treatment and can have a serious impact on quality of life and productivity at work, bringing undesirable direct and indirect costs to patients and society. Researchers cite the incidence of post-treatment cognitive problems as ranging from 18 to 78% [3]. The course and duration of treatment-related cognitive dysfunction is largely unknown. Frequencies are higher shortly following the completion of treatment [2, 4]. While one group of women shows (partial) recovery at 1 year post chemotherapy [1], others still experience cognitive dysfunction 10 to 20 years after treatment [5, 6].

Different candidate mechanisms for cancer therapy-related cognitive changes have been proposed and include direct neurotoxic effects of chemotherapeutic agents, indirect immune-mediated inflammatory processes, induced hormonal changes, and genetic predisposition [7]. Furthermore, cancer-related symptoms, such as fatigue, anxiety, depression and stress, can have an additional impact on cognitive performance [8]. Studies also show that cognitive impairment following chemotherapy is associated with structural and/or functional changes in the brain, more specific in the white matter microstructure which could be linked with decreases in cognitive performance [9, 10]. Changes in brain activation were observed both in the attention network during the execution of active tasks (e.g., multi-tasking) [11] as well as during rest in the default-mode network [12].

There is a great need for therapeutic interventions that can reduce cognitive symptoms after cancer treatment. So far, only a limited number of potential interventions targeting cancer-related cognitive impairment have been studied [13]. The most promising interventions so far appear to be cognitive training and physical activity [13, 14]. However, due to a lack of active control groups and the consideration of biological outcomes, it remains unclear to what extent these interventions are effective.

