## Methods/design

### Aim and objectives

The overall aim of the study is to examine whether MBI can improve cognitive functioning and quality of life for cancer patients after chemotherapy.

The objectives are as follows:
Investigate whether MBI improves cognitive functioning in comparison with both control conditionsDetermine the differences in both structural and functional changes in the brain within (longitudinal) and between the groups; andExplore whether changes in behavioral, psychological and biological outcomes, are associated with improvements in cognitive functioning

Our hypotheses are:
Both MBI and the physical training (active control condition) improve cognitive impairment compared to the TAU control conditionMBI is more effective than the active control condition for improving cognitive impairmentA mechanistic difference will exist between MBI and the active control condition based on brain imaging. More specifically, we expect a stronger impact in the salience and dorsal attention networks, the frontoparietal network and default mode network. These networks have been associated before with aspects of cognitive changes after chemotherapy treatment.

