**Brain imaging**				
High-resolution, T1-weighted imaging	Brain structure	x	x	x
Active fMRI during N-back task	Brain activation during N-back task	x	x	x
Resting-state fMRI	Brain connectivity	x	x	x
Diffusion MRI	White matter microstructure	x	x	x

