#### Active functional MRI (afMRI, duration ± 8 min)

Whole-brain, T2*-weighted EPIs, sensitive to blood oxygenation level dependent (BOLD) contrast will be used to acquire functional MRI (fMRI) scans while participants perform a memory task in the scanner. The fMRI task consists of a visual N-back sequential letter task used to assess working memory brain activation [46, 47]. Four conditions are tested: 0-back, 1-back, 2-back and 3-back in a blocked design. The 0-back control condition has a minimal working-memory load; participants need to decide if the current letter matches a single target letter that was specified before. In the 1-back condition, participants need to asses if the current letter matches the previous letter. During the 2-back (3-back) condition, participants need to assess whether the current letter matches the letter that has been presented 2-back (3-back) in the sequence. Participants practice the task before the scanning session. During the MRI scanning session, participants respond by pressing a button to indicate whether the item matches the target condition.

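### N-back activation comparisons are labelled confirmatory for the two cognition hypotheses (H1, H2) and exploratory for the imaging hypothesis (H3), so the label does not fit the hypotheses

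*Protocol article*

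**What the plan says.** All references are to the protocol article.

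- **Aim and objectives** lists three hypotheses. The first is that mindfulness and physical training each reduce cognitive impairment relative to usual care. The second is that mindfulness does so more than physical training. The third is that the two programmes differ in mechanism on brain imaging, where "we expect a stronger impact in the salience and dorsal attention networks, the frontoparietal network and default mode network".
- **Active functional MRI** describes the N-back task: "Four conditions are tested: 0-back, 1-back, 2-back and 3-back in a blocked design". It adds that "participants respond by pressing a button to indicate whether the item matches the target condition".
- **Table 2** gives the target concept of this scan as "Brain activation during N-back task".
- **Analysis plan** names two primary outcomes. One is "The difference in mean change scores from the baseline on the CFQ between groups"; the other is the corresponding change in attention-network connectivity. Functional activity during the N-back task is in the secondary list.
- **Data analysis** states that "Contrast images comparing pairs of working-memory load conditions (e.g., 3-back > 0-back") will be created for each patient, and that these "will be used in second-level analyses to assess differences between time points and groups (confirmatory tests for H1 and H2, exploratory test for H3").

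**The concern.** A confirmatory label tells the reader which results may be claimed as established. Here it joins an imaging contrast to hypotheses about cognition that have a direction, while the hypothesis that is actually about imaging is tested only in an exploratory way. A difference in activation shows that the groups differ in brain response. Whether that is better or worse cognition depends on a direction of benefit, and the article states none. If the label stands, a secondary imaging result could be reported as a confirmed finding on H1 or H2, beside the two outcomes declared primary for the trial.

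**Working it through.** There is no stated figure to reproduce. The check sets the parts of the article side by side.

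**Step 1: what each hypothesis is about.** Taking H1 to H3 in the order in which Aim and objectives lists them:

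| Hypothesis | Subject | Directional? | Status given to the N-back activation test |
|---|---|---|---|
| H1 | Cognitive impairment, each programme against usual care | Yes | Confirmatory |
| H2 | Cognitive impairment, mindfulness against physical training | Yes | Confirmatory |
| H3 | Brain-imaging mechanism, mindfulness against physical training | A larger effect in named networks; no sign for activation | Exploratory |

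The two rows marked confirmatory are the two that are not about imaging.

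**Step 2: is a direction of benefit given anywhere for activation?**

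- Background: "Changes in brain activation were observed both in the attention network during the execution of active tasks". This reports changes and gives no sign.
- Aim and objectives, H3: a stronger impact in certain networks, without saying whether that means more or less activation.
- Analysis plan: changes in activity, no sign.
- Data analysis: differences between time points and groups, no sign.

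None of the four places supplies the link from activation to improvement that a test of H1 or H2 would need.

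**Step 3: rank.** The Analysis plan places N-back activity below the CFQ and attention-network connectivity. Secondary rank does not by itself forbid a formal test. It does mean that the label gives H1 and H2 a confirmatory route outside the declared primary outcomes.

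**Step 4: does the reach of the bracket matter?** It closes the N-back sentence, which is also the last sentence of a paragraph on morphometry, diffusion and resting-state connectivity.

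- If it covers the N-back only, one secondary outcome carries the wrong label.
- If it covers the paragraph, the secondary structural, diffusion and connectivity maps carry it too. Those are likewise tested for differences between time points and groups.

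The mismatch remains on either reading and is larger on the second.

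**Context only.** Four load conditions give 4 × 3 / 2 = 6 possible pairwise contrasts, and one is named, as an example. The choice among them may well be fixed in a fuller document, so it is not counted here.

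**The case against.** The strongest reply has five parts.

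1. **H1 and H2 already have a proper test.** The CFQ is primary and measures cognitive failures, and Data analysis names the multilevel model, with false discovery rate control, as the confirmatory test of the intervention. This stands, and it limits the weight of the point. It does not explain why an activation contrast should also be confirmatory for the same hypotheses. False discovery rate control limits false claims but does not supply a direction of benefit.

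2. **No rule says that any difference confirms benefit.** A reader might infer that a group difference in either direction, in any region, would be counted as proof that mindfulness improves cognition. The article does not say so. It gives no decision rule for H1 or H2 based on activation, and a two-sided comparison read by its sign is ordinary practice. Contrast, region and direction may also be set in an analysis plan or full protocol that is not shown. This part stands in full; only the label, which the article itself fixes, is at issue.

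3. **A secondary outcome may be tested in a confirmatory way.** True. The fault is that the outcome is attached to the wrong hypotheses, not that it is tested.

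4. **Task performance.** A reader might also infer that the trial discards an objective measure, because N-back accuracy is in neither the outcome list nor Table 2. The documents do not support that. They say that participants press a button, but not whether the responses are stored, scored or dropped. The lists are visibly incomplete: quality of life is a secondary outcome in the Abstract and has its own measures section, yet is missing from both the Analysis plan list and Table 2. Objective cognition is covered by a four-domain neurocognitive battery that is a listed secondary outcome.

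5. **Numbering.** The labels H1 to H3 might have been meant to follow the three objectives, of which the second concerns the brain and the third is explicitly exploratory. That would ease part of the mismatch. The confirmatory label would still include the first objective, on cognitive functioning, and the letter H points to the hypotheses.

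**Conclusion.** The point holds as a mismatch between label and hypothesis. The N-back activation comparisons, and possibly the other voxel-wise comparisons in the same paragraph, are called confirmatory for two directional hypotheses about cognition and exploratory for the imaging hypothesis. N-back activity is secondary and has no stated direction of benefit, so a difference in it cannot alone confirm improved cognition.

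The consequence is limited to what may be claimed as confirmed. H1 and H2 keep a directional test through the CFQ, and no figure in the article allows the harm to be quantified. The verdict assumes that H1 to H3 follow the order of the listed hypotheses. It does not depend on which reading of the bracket is right.

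**What to change.** In Data analysis, delete the confirmatory label for H1 and H2 from the N-back activation analysis and from any other secondary imaging maps that the bracket was meant to cover. Assign these analyses to H3 as exploratory. State that confirmatory claims on H1 and H2 rest on the declared primary outcomes in the Analysis plan, with the CFQ carrying the directional claim about cognition. Attention-network connectivity keeps its rank as a declared primary outcome.

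The cost is a change of wording and one fewer route to a confirmatory claim. No visit, scan or sample size changes.

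Optionally, if the in-scanner button responses are stored, report N-back accuracy beside activation as an aid to interpretation. This adds a small analysis, and the main change does not depend on it.

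### If the correlations linking brain and inflammation measures to cognition are pooled over the three arms, treatment effects alone can produce an association; they should be adjusted for condition

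*Protocol article*

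**What the plan says.** The third objective in the protocol article (Aim and objectives) is to explore whether changes in behavioural, psychological and biological outcomes "are associated with improvements in cognitive functioning". Two analyses in the Data analysis section bear on it.

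- **Correlation.** One sentence lists the questionnaire scores, the neuroimaging maps, the neurocognitive test results and the inflammation markers, and ends: "will be investigated using correlation analysis". It does not mention condition, time point or change scores.
- **Mediation.** "To evaluate the process of change a mediation analysis will be performed". The method is described as follows: "Mediation will be tested (exploratory) by adding potential mediators (e.g., different mindfulness facets". The mediators enter the model together with other terms: "and their interaction with condition and time in the intervention model". Condition and time are therefore in this model. Mindfulness facets are the only mediators given as an example; brain and inflammation measures are not named.

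On design, the Randomization section says "Participants are randomized (1:1:1) to the control group or intervention groups", and the planned size is 40 per arm, 120 in all.

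**The concern.** Objective 3 is about whether the women whose biology changes are also the women whose cognition improves. In a three-arm trial, a correlation over all women has two components: the association among women in the same arm, and the fact that an effective arm moves several outcomes at once. The second exists even when the first is zero.

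The plan expects shifts of this kind. Hypothesis 1 has both active arms improving cognition relative to usual care, hypothesis 3 expects the two active arms to differ on brain imaging, and the Discussion proposes brain and immune pathways. The artefact is thus largest when the interventions work, and it would look like the mechanistic evidence the trial hopes to supply. Control of the false discovery rate does not remove it: that control allows for the number of tests, whereas here each pooled p-value is miscalibrated as a test of within-arm association.

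**Working it through.** **Plan's own figure.** There is none. The article gives no expected correlation, effect size or power for this analysis, and the sample size rests on the group sizes of earlier studies. The check therefore concerns the mechanism only.

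**Inputs from the article.** Three arms, 1:1:1, 40 per arm, 120 in total. The pilot's within-group effects (Background) are 0.93 with mindfulness and 0.12 with usual care; 0.93 − 0.12 = 0.81 is used as a rough proxy for a between-arm effect on cognition.

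**Assumptions.** All standardized effects below, including any use of 0.81; no dropout; one pair of scalar measures; within-arm SD of 1 and within-arm correlation of 0; two-sided 0.05 (the article states p < 0.05 for the imaging maps only). Scores are oriented so that a positive effect is an improvement.

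**Formula.** With arm means mX and mY and equal arms,

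pooled r = Cov(mX, mY) / √[(1 + Var mX)(1 + Var mY)].

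When both variables have the same arm means this is B/(1 + B), where B is the variance of the arm means.

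**Case consistent with hypotheses 1 and 2** (effects of 0.8, 0.4 and 0 on both variables). The mean is 0.4, so B = (0.16 + 0 + 0.16)/3 = 0.107 and r = 0.107/1.107 = 0.096. By Fisher's z, the standard error is 1/√117 = 0.0925 and 0.0967/0.0925 = 1.05. The chance of p < 0.05 is then P(Z > 1.96 − 1.05) plus a negligible lower tail, about 18%.

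**Smaller cases.** For an effect a on cognition and b on biology in the mindfulness arm only, Cov = 2ab/9, and the variances are 2a²/9 and 2b²/9. For a = 0.81 and b = 0.5: Cov = 0.090, and r = 0.090/√(1.146 × 1.056) = 0.082.

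Simulation of 20,000 trials of 3 × 40 gives:

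| Assumed effects, SD (mindfulness / physical training / usual care) | Pooled r by formula | p < 0.05, pooled | p < 0.05, adjusted for arm |
|---|---|---|---|
| None | 0 | 5.1% | 5.2% |
| 0.8 / 0.4 / 0 on both | 0.096 | 17.8% | 5.1% |
| 0.3 / 0 / 0 on both | 0.020 | 5.3% | 5.1% |
| 0.5 / 0 / 0 on both | 0.053 | 8.8% | 4.9% |
| Cognition 0.81 / 0 / 0, biology 0.3 / 0 / 0 | 0.050 | 8.4% | 5.1% |
| Cognition 0.81 / 0 / 0, biology 0.5 / 0 / 0 | 0.082 | 14.5% | 5.2% |
| Cognition 0.5 / 0 / 0, biology 0 / 0.5 / 0 | −0.026 | 6.1% | 5.1% |

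The critical |r| at n = 120 is 0.179, so the induced correlation in these cases is well below significance by itself; the harm lies in the shifted null. The mindfulness-only rows are there to show smaller effects. They set the effect of physical training on cognition to zero, which hypothesis 1 does not expect.

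**The case against.** Four points can be made against this.

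1. **Pooling is not stated.** The article says correlation analysis and no more. Partial and within-arm correlations are correlation analyses too, and the full protocol or SAP may settle the matter. This stands. A reader might infer that the plan commits to unadjusted correlations over all 120 women; the text does not say so, and the point is conditional on it.
2. **Correlation is not the only process analysis.** A reader might infer that nothing else addresses objective 3. The mediation model does address it, with condition and time included, and the Discussion mentions possible mediators after listing brain and immune pathways. This stands as to the model's existence. It does not show that brain or inflammation measures will enter it, since the Data analysis section gives only mindfulness facets as an example.
3. **Pooled or adjusted is a choice of estimand.** Objective 3 does not specify a within-arm association. If treatment acts through biology, variation between arms is part of the signal, and adjusting removes it. This stands in part: a pooled correlation is a legitimate description, but it cannot separate that signal from an arm that moves two unrelated outcomes.
4. **The size depends on the scenario.** This also stands. Worse cases can be built, such as equally large effects in both active arms or a 1 SD effect with mindfulness alone. The first conflicts with hypothesis 2 and the second with hypothesis 1, so neither is used here.

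A reader might add that change scores share baseline error. That does not follow for two different instruments with separate baselines unless their measurement errors are correlated, and the article gives no ground for that.

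**Conclusion.** The point holds in conditional form and is minor. For brain and inflammation measures, an unqualified correlation is the only method named for relating them to cognition, and it contains no term for condition, unlike the article's own mediation model. If the arms are pooled and both variables respond to treatment, the false-positive rate for a within-arm association is about 18% under assumed effects of 0.8/0.4/0 SD on both. It is about 5% to 9% for a mindfulness-only effect of 0.3 to 0.5 SD on both, and about 8% to 15% for 0.81 SD on cognition with 0.3 to 0.5 SD on biology. With modest biological effects the inflation is small.

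These figures rest on assumed effects, complete data and no within-arm association. The analysis is exploratory and the primary comparisons between arms are not affected.

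**What to change.** In the Data analysis section, replace the correlation sentence with one to this effect: the change in each cognitive outcome will be related to the change in each questionnaire, imaging or inflammation measure by partial correlation or regression adjusted for condition, and the estimates within each arm will also be shown.

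This uses data already collected. Adjusting for three arms costs two degrees of freedom: on Fisher's z scale the standard error goes from 1/√117 = 0.0925 to 1/√115 = 0.0933. The within-arm estimates are less precise (1/√37 = 0.164 with 40 women) and should be read as descriptive.
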